The clinical trial is overseen by the trial steering committee (TSC), composed of [name] (coordinating investigator, Grenoble-Alpes University Hospital), [name] (medical coordinator of CIC-IT Grenoble), [name] (president of IMACTIS®), [name] (coordinator of CIC-IT Garches) and [name] (investigator, Rennes University Hospital). The TSC has responsibility for monitoring the patient enrolment rate at each centre and modifying the proposed statistical analysis framework if necessary following the interim analysis.

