To ensure the correct progress of the trial and to verify that the proposed statistical analysis framework is appropriate, an interim analysis of the primary outcome will be performed once the first four participating hospitals have finished patient enrolment. To maintain a global cut-off of 5% for the final analysis, the interim analysis will be carried out using a cut-off of 0.1%. The results of the interim analysis will be considered by the TSC to judge whether the statistical analysis framework requires modifying. When patient enrolment is finished, the final monitoring is completed and the coherence of the recorded data is verified, the database will be frozen, and the final statistical analysis of the data will be carried out.

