Estimating the loss to follow-up and the withdrawal of consent to be 4%, a minimum of 200 participants will be enrolled per group. Because the study was initially designed with the participation of eight hospitals, and to minimise a centre bias, the number of patients to be included per hospital was set at 50 ± 15. After inclusion had begun, a ninth centre requested to participate in the study. Because inclusion had already begun, the number of inclusions per centre was maintained, and the maximum sample size was defined to be 500. The study protocol was therefore modified, and the modifications were approved by the French Health Authority (Agence Nationale de Sécurité des Médicaments et des Produits de Santé) and the relevant ethics committee (Comité de Protection des Personnes, Sud-Est V, France). The sample size calculations were carried out using nQuery Advisor® 7.0 software (Statistical Solutions, Cork, Ireland) with the method ‘upper confidence limit for difference in proportions (simulation)’ [34] for the safety and efficacy criteria and Noether’s method ‘sample size determination for some common nonparametric statistics’ [35] for the performance criterion.

For the statistical analysis of the data, because non-inferiority tests are used to evaluate the safety and efficacy criteria, a PP analysis will be carried out on the data, comparing the 90% two-sided confidence interval of the difference between the proportions with the non-inferiority cut-off. Conversely, because a superiority test is used to evaluate the performance criterion, an ITT analysis will be carried out on this data, comparing the means of the two groups using Student’s *t* test or the non-parametric Mann-Whitney *U* test. For all calculations, a threshold of *p* < 0.05 is considered significant.

For the secondary outcome analysis, the means of the two groups will be compared using Student’s *t* test or the non-parametric Mann-Whitney *U* test for each outcome. Furthermore, subgroup analyses according to the difficulty of the procedure will be carried out. ITT and PP analyses will be carried out for the secondary outcomes to ensure the robustness of the results [36].

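### The steering committee, which includes the manufacturer's president and two investigators, receives the interim primary-outcome result and may then modify the statistical framework without a stated limit; the 0.1% interim cut-off does not cover such a change

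*Protocol article*

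**What the plan says.** The interim paragraph of *Methods/design, Methods* (the last one before *Statistical analysis*) says that "an interim analysis of the primary outcome will be performed once the first four participating hospitals have finished patient enrolment". On error control it says: "To maintain a global cut-off of 5% for the final analysis, the interim analysis will be carried out using a cut-off of 0.1" per cent. On the use of the result it says: "The results of the interim analysis will be considered by the TSC to judge whether the statistical analysis framework requires modifying".

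*Study design and setting* gives the TSC the matching authority, namely responsibility for "modifying the proposed statistical analysis framework if necessary following the interim analysis". It lists five members. Three of them matter here: the "president of IMACTIS", the "coordinating investigator, Grenoble-Alpes University Hospital" and the "investigator, Rennes University Hospital". The other two are coordinators in the CIC-IT network.

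*Statistical analysis* sets the final threshold at p < 0.05 throughout. Safety and efficacy are judged by a two-sided 90% confidence interval in the per-protocol set. Performance is tested in the intention-to-treat set by a t test or a Mann-Whitney test. At least 200 patients per group are to be enrolled, and "the maximum sample size was defined to be 500".

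**The concern.** The primary outcome is defined as a comparison of the two groups, so applying a 0.1% cut-off to it produces an arm comparison. A pooled review would need no cut-off. Read together, the two sections hand that comparison to a committee that includes the device's commercial owner and two people running the trial, and let the committee revise the confirmatory analysis afterwards.

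The article says that the 0.1% cut-off preserves the global 5%. That argument covers one risk, an additional chance to declare success early. It does not cover a margin, test, analysis set or sample size chosen with the arm difference in view. Modifying the framework is the use that the article gives for the interim result, so the stated error control does not address the use to which the look is put. What is at stake is whether each component's 5% level, and so the claim of clinical benefit, can be defended if any change follows the look.

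**Working it through.** **Inputs from the article.** Interim level 0.001 and final level 0.05. Each hospital enrols 50 ± 15, so four hospitals give 4 × 35 = 140 to 4 × 65 = 260 patients. Total N is 400 to 500. The information fraction t therefore runs from 140/500 = 0.28 to 260/400 = 0.65. The safety margin is 7 points on an assumed 5% rate.

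**1. The article's own claim, with no change after the look.** The interim and final statistics are bivariate normal with correlation √t. Overall error = 1 − P(neither look rejects), with the interim tested at 0.001 and the final at 0.05.

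| t | one-sided | two-sided |
|---|---|---|
| 0.28 | 0.05044 | 0.05054 |
| 0.40 | 0.05027 | 0.05036 |
| 0.50 | 0.05016 | 0.05022 |
| 0.65 | 0.05004 | 0.05007 |

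The excess is at most about 0.05 percentage points. If nothing else changes, the cut-off does what the article says.

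**2. Total N chosen after seeing the interim result.** Assume a look at n₁ = 200 patients and a final test without adjustment at critical value c. Given interim statistic z₁ and second-stage size n₂, the chance of rejecting in the upper tail is 1 − Φ((c√(n₁+n₂) − z₁√n₁)/√n₂); the two-sided version adds the lower tail. Taking the most favourable n₂ for each z₁ and averaging over z₁ ~ N(0,1) gives the worst case:

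| Permitted total N | one-sided | two-sided |
|---|---|---|
| 400 to 500 | 5.4% | 5.5% |
| 235 to 500 | 7.0% | 7.3% |
| no limit | 11.3% | 11.1% |

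The second row assumes that the trial could end after one more hospital at its minimum (200 + 35 = 235), which is below the planned minimum of 400. The third row is only a ceiling for this kind of change.

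**3. Safety margin widened only after an unfavourable look.** Take true rates of 12% and 5%, the boundary of the 7-point margin. Non-inferiority is claimed if d + 1.645 × √(p₁(1−p₁)/n + p₂(1−p₂)/n) is below the margin, with n = 200 per group. With the margin left at 7 points, the exact binomial chance of a false claim is 5.5%. Assume a look at 100 per arm and a wider margin only if the observed difference is at least 7 points. The chance of a false claim then becomes 6.1% with an 8-point margin and 7.6% with a 9-point margin. Other triggers give other values.

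**4. Choice between t test and Mann-Whitney by the interim p-values.** In a simulation with assumed negative-binomial scan counts (200 per arm, 4,000 runs), the error is 5.4%. The standard error is √(0.054 × 0.946/4000) = 0.36 points, so this is not clearly above 5% and carries little weight.

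**The case against.** The case on the other side has substance, and several stronger readings fail.

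- **The 5% level is already lost.** It is not. Step 1 shows that it holds if the framework stays as planned, and the article does not say that a change was or will be made.
- **Moving the margin takes the safety error to 10.7% or 18.7%.** Those are the chances of passing an 8- or 9-point margin at true rates of 12% and 5% with 200 per group. No interim look enters that calculation; a wider margin set at the outset would give the same figures. The article nowhere proposes moving the margin, which it derives from published complication thresholds.
- **The 400 to 500 range is a lever for the committee.** *Statistical analysis* attributes the maximum to a ninth hospital joining while recruitment per hospital was kept. It does not link N to the interim result.
- **Knowledge of the result will distort difficulty ratings.** Difficulty is rated on the initial scan and recorded before randomisation, so the rating cannot depend on a known allocation. Conversions to conventional guidance come after allocation and remove patients from the per-protocol set, so that route is more plausible. But the article does not say that results reach operators, or which hospitals are the first four.
- **No action is attached to crossing 0.1%.** An article may leave that to the full protocol.

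Two defences stand in part. First, benefit requires all three criteria, so loosening one need not carry its full inflation into the overall conclusion. That helps little when a device clearly meets two criteria and truly fails the third. Second, the ninth-centre modification went to the health authority and the ethics committee, and a later change might too. Such review is an external control, but it does not preserve the type I error.

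The article does not state outright that the TSC sees results by arm. That is an inference from the cut-off. If only pooled data were meant, the cut-off has no function and the wording still needs correcting.

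**Conclusion.** The point holds in a limited form. The article gives an interim result that must be read as comparative to a committee that includes the manufacturer's president and two investigators, and lets that committee modify the statistical framework with no stated limit. The 0.1% cut-off protects the global 5% only while the final analysis is unchanged.

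The inflation depends on the change made, and the documents cannot fix it. The illustrations are modest to moderate: about 5.4% for N within the planned range, about 7.0% for the wider range, and about 6.1% to 7.6% (against 5.5%) for a margin widened after an unfavourable look. They rest on an assumed look at 200 patients (100 per arm), an unadjusted final test and, for the margin, the 7-point trigger. A reader might infer that the manufacturer is expected to alter the margin or that the error rate is already compromised. The text supports neither. It supports only that nothing stated prevents a change informed by the arm comparison.

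**What to change.** State that any change of framework by the TSC rests only on pooled data without arm (overall complication rate, overall target-reached rate, scan-count distribution, missing-data and conversion rates) and is dated before any arm comparison is seen.

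If the 0.1% comparative look is kept, a statistician outside the TSC should run it and pass on only a prespecified continue/stop message. Margins, analysis sets, tests and final N should be fixed before the look.

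*Trial status* reports enrolment from December 2013 with completion expected before the end of June 2017, so the look may already have taken place. In that case, report any later change as made with knowledge of the arm comparison, and keep the framework in force before the look as the primary analysis.

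If the look is still to come, the cost is a change of wording and a simpler report for the committee. The downside is that the TSC does not see the arm difference during the trial.

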### Statistical analysis

The number of patients to be enrolled in the study is calculated as the maximum of the values calculated for each of the three different criteria (safety, efficacy and performance) that constitute the primary outcome, with the alpha level set to 5%. The calculations are performed as follows for each of the three criteria:
*Safety*: The suggested threshold for all major complications resulting from percutaneous drainage or biopsy procedures is 10% [31, 32]. The threshold is increased to 20% for lung procedures [33]. Because one of the participating hospitals is a referral centre for lung procedures, it has been decided to define the threshold for all major complications as 12% for this study (calculated as the average threshold across the centres, 12 = (10 × 8 + 20 × 1)/9, rounded up to the nearest whole number). Considering an initial complication rate of 5% in each of the groups, a sample size of 384 patients (192 in each of the experimental and comparator arms of the trial) will be sufficient to demonstrate non-inferiority between the groups, respecting a non-inferiority cut-off δ = 7%, with 90% power and a 5% significance level.
*Efficacy*: The minimum threshold for intervention success is 80%. Considering an initial success rate of 91% in each of the groups, a sample size of 380 patients (190 per group) will be sufficient to demonstrate non-inferiority between the groups in terms of success, respecting a non-inferiority cut-off δ = −10%, with 90% power and a 5% significance level.
*Performance*: Considering that use of the navigation system will decrease the number of control scans acquired by 20% compared with conventional procedures (estimated from previous clinical trial), a sample size of 222 patients (111 per group) will be sufficient to demonstrate superiority in the NAV group compared with the CT group in terms of a decrease in the number of control scans acquired, with 90% power and a 5% significance level.

Estimating the loss to follow-up and the withdrawal of consent to be 4%, a minimum of 200 participants will be enrolled per group. Because the study was initially designed with the participation of eight hospitals, and to minimise a centre bias, the number of patients to be included per hospital was set at 50 ± 15. After inclusion had begun, a ninth centre requested to participate in the study. Because inclusion had already begun, the number of inclusions per centre was maintained, and the maximum sample size was defined to be 500. The study protocol was therefore modified, and the modifications were approved by the French Health Authority (Agence Nationale de Sécurité des Médicaments et des Produits de Santé) and the relevant ethics committee (Comité de Protection des Personnes, Sud-Est V, France). The sample size calculations were carried out using nQuery Advisor® 7.0 software (Statistical Solutions, Cork, Ireland) with the method ‘upper confidence limit for difference in proportions (simulation)’ [34] for the safety and efficacy criteria and Noether’s method ‘sample size determination for some common nonparametric statistics’ [35] for the performance criterion.

For the statistical analysis of the data, because non-inferiority tests are used to evaluate the safety and efficacy criteria, a PP analysis will be carried out on the data, comparing the 90% two-sided confidence interval of the difference between the proportions with the non-inferiority cut-off. Conversely, because a superiority test is used to evaluate the performance criterion, an ITT analysis will be carried out on this data, comparing the means of the two groups using Student’s *t* test or the non-parametric Mann-Whitney *U* test. For all calculations, a threshold of *p* < 0.05 is considered significant.

For the secondary outcome analysis, the means of the two groups will be compared using Student’s *t* test or the non-parametric Mann-Whitney *U* test for each outcome. Furthermore, subgroup analyses according to the difficulty of the procedure will be carried out. ITT and PP analyses will be carried out for the secondary outcomes to ensure the robustness of the results [36].

If a patient withdraws consent before random assignment to a group, that patient is removed from the study and is excluded from the statistical analysis. If other situations occur after random assignment to a group (consent is withdrawn, the protocol is not respected, the radiologist chooses to use conventional CT guidance rather than the navigation system for a patient in the NAV group, or the radiologist changes the original procedure prescribed), the patient concerned will be excluded from PP analyses. For the ITT analyses, missing data in the NAV group will be filled using the worst values for procedures of the same difficulty rating in the same centre in the NAV group, whereas missing data in the CT group will be filled using the best values for procedures of the same difficulty rating in the same centre in the CT group. If after random assignment to the NAV group the navigation system is unavailable, the patient remains in the study, and the procedure is performed under conventional CT guidance; the patient will be excluded from PP analyses. For the ITT analyses, the patient remains in the NAV group, with missing data filled using the worst values for procedures of the same difficulty rating in the same centre in the NAV group.

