For this trial, a maximum of 500 patients for whom a percutaneous procedure in the thoraco-abdominal area under CT guidance has been prescribed will be enrolled in the study across the nine participating hospitals. The trial is structured as a standard two-arm, parallel-design, individually randomised trial*.* Patients are randomly assigned to the experimental arm of the trial in which procedures are carried out using navigation assistance (the NAV group), where the procedures are carried out using navigation assistance supplied by the medical device under evaluation (IMACTIS-CT®), or to the active comparator arm of the trial in which procedures are carried out guided by conventional CT (CT group), where the procedures are carried out under conventional CT guidance. The randomisation is stratified by centre and by the expected difficulty of the procedure. The assignment is open label for both the radiologist and patient.

Because a previous clinical trial has already demonstrated improved needle placement accuracy in navigation-assisted procedures using the IMACTIS-CT® device (4.1 mm [2.7–9.1]) compared with conventional procedures (8.9 mm [4.9–15.1], *p* < 0.001) according to ITT analysis [29], the aim of this trial is therefore to evaluate the clinical benefit of the navigation system. The primary outcome is a combined criterion composed of three different criteria which assess, respectively, the safety, efficacy and performance of navigation-assisted CT-guided procedures by comparing the results obtained in the navigation-assisted group with those obtained in the conventional group. The criteria will be evaluated by a blinded expert committee. It will be determined that the navigation system represents a clinical benefit if non-inferiority in terms of safety, efficacy and superiority in terms of performance is obtained in the navigation-assisted group with respect to the conventional group. Also evaluated, in terms of secondary outcomes, are (1) the duration of the procedure, (2) the satisfaction of the operator and (3) the irradiation dose delivered, with (4) subgroup analysis according to the expected difficulty of the procedure, as well as an evaluation of (5) the usability of the device.

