The president of IMACTIS® and/or an application engineer from the company will install the navigation system at each of the nine participating hospitals and will then provide training for the participating radiologists on how to use the system. Training is obligatory before any radiologist is authorised to carry out a navigated procedure on a patient enrolled in the trial. Training is first conducted using phantom models and is then continued on one or more patients who are not enrolled in the trial. The number of training procedures carried out is noted to minimise the learning curve bias.

For this clinical trial, the foreseeable risks are those associated with conventional CT-guided interventional radiology. No foreseeable supplementary risk is expected from the use of the navigation system. Contraindications are explicitly stated in the inclusion and exclusion criteria. Furthermore, because the navigation system is a passive medical device, the radiologist can choose to stop using the system at any moment, in particular in case of failure or malfunction of the system, and complete the procedure under conventional CT guidance, without any influence on the procedure or patient.

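### Safety and efficacy non-inferiority are tested only per protocol, and two of the per-protocol exclusions can arise only in the navigation arm, so the test can be biased towards non-inferiority, most clearly for safety

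*Protocol article*

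**What the plan says.** All references are to the protocol article, Methods/design.

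- **Decision rule** (Study design and setting). Clinical benefit is concluded if "non-inferiority in terms of safety, efficacy and superiority in terms of performance is obtained in the navigation-assisted group".
- **Analysis set for safety and efficacy** (Statistical analysis). "because non-inferiority tests are used to evaluate the safety and efficacy criteria, a PP analysis will be carried out on the data". The test consists of "comparing the 90% two-sided confidence interval of the difference between the proportions with the non-inferiority cut-off".
- **Analysis set for performance** (Statistical analysis). "because a superiority test is used to evaluate the performance criterion, an ITT analysis will be carried out on this data".
- **Where both sets are planned** (Statistical analysis). "ITT and PP analyses will be carried out for the secondary outcomes to ensure the robustness of the results". Safety and efficacy are not secondary outcomes, so this does not reach them.
- **PP exclusions** (Statistical analysis). One listed reason is that "the radiologist chooses to use conventional CT guidance rather than the navigation system for a patient in the NAV group". A second concerns equipment: "If after random assignment to the NAV group the navigation system is unavailable, the patient remains in the study". That patient is treated under conventional guidance and left out of PP. Withdrawn consent, departures from the protocol and a changed procedure are also grounds, in either arm.
- **When navigation may be stopped** (Materials). "the radiologist can choose to stop using the system at any moment, in particular in case of failure or malfunction of the system".
- **Endpoints** (Methods). Safety counts major adverse events attributable to needle insertion. Efficacy counts targets reached, meaning that the needle is placed well enough for the next step. Neither definition requires the needle to have been guided by navigation.

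**The concern.** Reverting to CT guidance and system unavailability are events after randomisation that only NAV patients can have. The first is decided by an operator who knows the allocation, and the Materials section links stopping to failure or malfunction of the device. If such procedures have worse outcomes than the rest, removing them improves the NAV arm and leaves the CT arm untouched.

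PP analysis is usually preferred for non-inferiority because an all-randomised analysis can dilute a real difference. Here PP can be the less conservative set, and no other set is named for these two criteria. A device with too many major complications could be declared non-inferior because some of those complications were removed from the comparison. The article already has rules for keeping such patients in NAV under intention to treat, but it does not apply that analysis to safety or efficacy.

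**Working it through.** **Inputs from the article.** Complication rate 5% per group, margin 7 points; success rate 91% per group, margin 10 points; 90% two-sided interval (one-sided 5%); 192 per group for safety; at least 200 per group after a 4% allowance.

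**Assumed inputs.** The share of NAV procedures abandoned and the outcomes of those patients. The documents give neither.

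**Step 1: the plan's own figure.** Unpooled formula: n = (1.645 + 1.282)² × (2 × 0.05 × 0.95) / 0.07² = 8.564 × 0.095 / 0.0049 ≈ 166.0, so 167 per group. With a continuity correction it is 194, close to the stated 192. Exact enumeration at 192 per group gives power 0.899 with the correction and 0.927 without. The allowance gives 192 / 0.96 = 200. The plan's figure reproduces at one-sided 5%.

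**Step 2: safety, NAV truly at the margin.** Let c = 0.12 be the NAV complication rate, with CT at 0.05. Let f be the share of complicated NAV procedures excluded from PP, with no uncomplicated ones excluded.

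- Excluded fraction of the NAV arm = f × c
- PP complication rate = c(1 − f) / (1 − c × f)
- False-claim rate = exact binomial probability that the upper limit of the 90% Wald interval for NAV − CT is below 0.07, with CT n = 200

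| f | Excluded share of NAV | NAV n in PP | PP rate in NAV | False-claim rate |
|---|---|---|---|---|
| 0 | 0 | 200 | 12.0% | 5.5% |
| 10% | 1.2% | 198 | 0.108/0.988 = 10.9% | 12% |
| 25% | 3.0% | 194 | 0.090/0.970 = 9.3% | 29% |
| 50% | 6.0% | 188 | 0.060/0.940 = 6.4% | 77% |

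The first non-zero row is about two patients (200 × 0.012 = 2.4).

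**Step 3: a different safety scenario.** Suppose 20% of NAV procedures are abandoned with a 40% complication rate, and the other 80% match CT. The whole arm is at 0.8 × 5% + 0.2 × 40% = 12%, exactly at the margin. With 192 randomised per group, PP claims non-inferiority with probability 0.89 and the all-randomised analysis with 0.055. This is an extreme case. Below 0.07/0.95 = 7.4% abandonment, the abandoned patients alone cannot bring the arm to the margin.

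**Step 4: efficacy.** Apply the same calculation with 81% NAV success against 91%, and treat every converted patient as a failure.

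- A quarter of failures excluded (0.25 × 19% = 4.75% of NAV): PP success 0.81/0.9525 = 85.0%, non-inferiority claimed 35% of the time.
- Half excluded (9.5% of NAV): PP success 0.81/0.905 = 89.5%, claimed 87% of the time.

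Under the protocol's endpoint, however, a target reached after conversion counts as reached. If converted patients reach it at the planned 91%:

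- All-randomised success is 0.81 + 0.0475 × 0.91 = 85.3%, or 0.81 + 0.095 × 0.91 = 89.6%.
- The all-randomised analysis then claims non-inferiority 39% or 90% of the time.
- The true deficits are 5.7 and 1.4 points, inside the 10-point margin, so these are not false claims.

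The efficacy bias therefore lies anywhere between none and the 35% and 87% figures, depending on what happens after conversion.

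**The case against.** **PP is the convention for non-inferiority.** This stands as a reason to include PP, and the article invokes it. It does not justify PP alone when exclusions specific to one arm can remove that arm's bad outcomes.

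**A robustness analysis is often left to the analysis plan.** This stands in part: that plan is not shown and may add one. But the article does not leave the set open. It names PP for these criteria, gives the reason and lists the exclusions.

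**The mechanism is partly conjecture.** This stands. Nothing in the article says that operators abandon navigation because a complication has begun or the target is being missed. The reason it singles out is system failure or malfunction, and reversion could be decided before insertion. If abandoned patients fare like the others, there is no bias, only some loss of power.

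**The exclusions are limited.** This stands in part. Before randomisation the system is checked as available and working and the procedure as maintained. Consent withdrawal, protocol departures and changes of procedure apply to both arms. Only reversion and unavailability are confined to NAV.

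**Stronger readings.** A reader might infer that device failures as such leave the NAV arm, and that the 35% and 87% efficacy figures are false-claim rates under this protocol. The documents do not support that, because the efficacy endpoint is met however the needle was guided. A reader might also infer that every abandonment should count as an efficacy failure in the main analysis. That would change a primary endpoint.

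**Conclusion.** The point holds as a flaw in a stated rule. Two of the three deciding criteria rest on PP alone, and that set has two NAV-only exclusions that can be related to device performance. The direction of any such bias is towards non-inferiority.

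For safety, the nominal 5% error becomes about 12%, 29% or 77% if 10%, 25% or 50% of complicated NAV procedures are excluded. This assumes a NAV arm exactly at the margin, 200 per group, and no exclusion of uncomplicated procedures. The shares are illustrative; the article supports neither a particular rate nor a conclusion that bias will occur. For efficacy no single size can be given, because it turns on outcomes after conversion. The quoted rates are per criterion; a claim of clinical benefit also needs superior performance, but that test does not examine safety or efficacy.

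**What to change.** 1. Analyse safety and efficacy in all randomised patients in their assigned arm, with the protocol's own endpoint definitions, in addition to PP. Claim non-inferiority only if both 90% confidence intervals clear the margin.
2. Add a sensitivity analysis for efficacy that scores abandoned navigation as target not reached.
3. Tabulate PP exclusions by arm and reason.

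**Cost.** One extra analysis on data already collected: a research assistant attends every procedure, and all adverse events are recorded. The claim becomes somewhat stricter. If the arms are truly equal and abandonment is unrelated to outcome, safety power at 192 per group is 0.927 in all randomised patients and 0.918 in PP with 10% of NAV excluded; requiring both cannot exceed the lower figure.

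**Why item 2 is not the main rule.** With both arms truly at 91% and 200 per group, scoring every abandonment as not reached cuts power from 97% to 77%, 54% or 21% at assumed abandonment rates of 3%, 5% or 8%, even when abandonment has nothing to do with outcome.
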